## Assignment of interventions: allocation

### Sequence generation {16a}

#### Randomization and allocation concealment

Infants will be randomly assigned in a 1:1 ratio with variable block sizes. Randomization lists will be stratified by center and gestational age (26 + 0–27 + 6 and 28 + 0–29 + 6 weeks). Sequentially numbered, sealed, opaque envelopes indicating the study group will be prepared. Provision of randomization envelopes will be done by an independent institution not involved in patient recruitment.

### Concealment mechanism {16b}

Please see the “Sequence generation {16a}” section.

#### Implementation {16c}

Please see the “Sequence generation {16a}”section.

### Assignment of interventions: blinding

#### Who will be blinded {17a}

Blinding of doctors, nurses, and parents for the intervention is not possible in this study.

#### Procedure for unblinding if needed {17b}

Please see the “Who will be blinded {17a}” section.

## Data collection and management

### Data management plan, quality assurance, and monitoring

A data management plan will be written describing the whole flow of the study data. Documentation of study data will be done by the local principal investigator via eCRF within a web-based study database. Source data will remain within the study sites. Quality and correctness of the study data will be ascertained by GCP-conform monitoring of the study. Monitoring will be done on a risk-adapted basis and will include remote and on-site monitoring of the data by trained monitors.

### Plans for assessment and collection of outcomes {18a}

Please see the “Study procedures, examination methods, and outcome assessment” section.

### Plans to promote participant retention and complete follow-up {18b}

#### Data management {19}

Please see the “Data management plan, quality assurance, and monitoring” section.

#### Confidentiality {27}

##### Plans for collection, laboratory evaluation, and storage of biological specimens for genetic or molecular analysis in this trial/future use {33}

To date, no sampling of biological material is planned during the study.

## Statistical methods

### Statistical analysis {20a}

The following analysis populations are defined within this study:
*Intention to treat population*Consists of all patients included into the study of whom written parental consent was obtained and not withdrawn.*Safety population*The safety population is identical to the intention to treat population and consists also of all patients included into the study of whom written parental consent was obtained and not withdrawn.*Per protocol population*Patients fulfilling at least one of the following criteria will be excluded from the per protocol-population:
PEEP level is not documented or not between 3 and 5 cmH_2_O—if the infant is in the low PEEP group—or 6–8 cmH_2_O—if it is randomized in the high PEEP group—for more than 10% of time during the intervention period.Intubation within the first 10 min after birth and invasive mechanical ventilation for more than 1 h.

The analysis of the primary endpoint will be done by Cochran-Mantel-Haenszel test stratified for treatment groups. The primary endpoint will be re-evaluated by Cochran-Mantel-Haenszel test adjusted for gestational age group (26 + 0–27 + 6 versus 28 + 0–29 + 6 weeks) and center. If the final number of centers does not allow adjustment for single centers, centers will be grouped. The grouping of centers will be justified within the statistical analysis plan. All secondary endpoints will be compared by Cochran-Mantel-Haenszel test or Student’s *t* test. In case of non-normally distributed data, Student’s *t* test will be replaced by Wilcoxon-Mann-Whitney test. The distribution of severity of BPD will be compared between the treatment groups by generalized logit model. Clinical and demographic characteristics of maternal and neonatal data will be described by mean and standard deviation, median, quartiles and minimum/maximum or rate and percentage. The analysis of the follow-up endpoints will be specified in an amendment to the study protocol before start of the 2- and 5-year follow-up. In case of more than 10% missing values concerning the primary endpoint, a worst case/best case analysis for this endpoint will be performed in the intention to treat population as sensitivity analyses and results will be included into the final report. No sensitivity analyses will be done for secondary or further relevant endpoints. In case of more than 20% missing values concerning one of the endpoints until PMA36, this endpoint will only be tabulated but no statistical test will be performed due to risk of biased data.

All analyses will be predefined in a statistical analysis plan written before end of study and completion of data monitoring. Only the analysis of the primary outcome variable in the intention-to-treat population will be considered confirmatory on a level of significance of 0.05. All other analyses including the analysis of the primary outcome variable in the per protocol population and all analyses concerning secondary endpoints will be considered exploratory only.

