### Criteria for discontinuing or modifying allocated interventions {11b}

#### Individual preterm end of study intervention

##### For the individual patient

Treatment may be terminated for safety concerns by the attending physician together with the local principal investigator or according to the wish of the patient’s parents or legal representatives at any time. The reasons for premature termination of the study intervention have to be documented in the study database. These patients will be maintained in the study, study visits have to be done as planned, and their outcome will be included in the intention-to-treat analysis.

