### Recruitment {15}

#### Recruitment and study duration

Patients will be recruited in 6 German tertiary care neonatal centers. Results of a systematic surveillance protocol prior to study start yielded a number of 240 eligible preterm infants meeting the inclusion criteria annually in all participating centers. Based on the assumption that approximately 50% of eligible infants will be included in the study, the recruitment period is expected to be 27 months. All preterm infants who are born at the participating institutions with a gestational age at birth of 26 + 0/7 to 29 + 6/7 weeks have to be screened for the study. Each screened patient is given a patient screening number (PSN) in consecutive order according to the screening log in the investigator site file (ISF). This number is the overall identifier of the pseudonymized patient throughout the study. For every screened patient, a screening form has to be filled in the electronic case report form (eCRF). This enables the documentation of non-biased recruitment. The screening eCRF form will document presence and absence of inclusion and exclusion criteria, whether the parents had been approached and whether informed consent was given, but will not document any patient identifiers. Outborn infants will not be screened as study treatment has to start immediately after birth. Patients can only be enrolled into the study if informed written consent was given by both parents/guardians (by the only parent/guardian in case of single-parent/guardian families) before birth. In case parents are less than 18 years of age, the relevant legal guardian(s) of the child has/have to sign the informed consent. Following multiple birth, parents are asked whether the infants could be randomized separately. If parents wish randomization to one study arm, the second child is treated like the randomized child, but not recruited to the study. The parental wish is documented on the informed consent form.

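### Formal withdrawal of parental consent at any time after randomisation removes an infant from the intention-to-treat and safety populations, with no rule for data already collected

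*Protocol article*

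**What the plan says.** Statistical analysis {20a} defines the ITT population as "all patients included into the study of whom written parental consent was obtained and not withdrawn". It adds: "The safety population is identical to the intention to treat population". Neither definition mentions randomisation or the timing of a withdrawal, and neither separates ending treatment, ending follow-up and refusing the use of data.

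The same section gives this population its weight: "Only the analysis of the primary outcome variable in the intention-to-treat population will be considered confirmatory on a level of significance of 0.05". Its safeguard against missing outcomes is conditional: "In case of more than 10% missing values concerning the primary endpoint, a worst case/best case analysis for this endpoint will be performed". That analysis runs inside the ITT population.

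Three other places bear on the point:

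- Recruitment {15}: "Patients can only be enrolled into the study if informed written consent was given by both parents/guardians", and this must happen before birth.
- Who will be blinded {17a}: "Blinding of doctors, nurses, and parents for the intervention is not possible in this study".
- Criteria for discontinuing {11b}: where treatment is stopped for safety or at the parents' wish, the infant stays in the study and "their outcome will be included in the intention-to-treat analysis". Infants at a centre that is closed early are treated the same way.

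**The concern.** An ITT comparison is protected by randomisation only if membership is fixed at randomisation. Here it also depends on something that can happen later, decided by people who know the arm and can see how the infant is doing. Consent is given before birth and treatment starts at birth, so a withdrawal for a treated infant necessarily follows exposure.

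The primary endpoint closes at 120 h, but follow-up runs to 36 weeks postmenstrual age, discharge, 24 months and 60 months. Read as written, a withdrawal during later follow-up would also remove a primary outcome already recorded. Because the safety population is identical, a death or serious event in that infant would leave the safety tables too.

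If withdrawal is related to both outcome and arm, the confirmatory comparison is biased. The worst/best-case analysis cannot show this, because an infant outside the ITT population is not a missing value within it.

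**Working it through.** **Inputs from the protocol.** Sample size {14}: failure rates 50% and 30%, significance level 0.05, power 80%, 103 per group, 5% drop-out, 216 in total. Sequence generation {16a}: 1:1 allocation, hence 108 per arm. Sidedness is not stated; two-sided is assumed because it reproduces the plan's figure.

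**The plan's own figure.**

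- Uncorrected: n = [1.960·√(2·0.4·0.6) + 0.842·√(0.5·0.5 + 0.3·0.7)]² / 0.2² = 93.0 per group.
- Continuity-corrected: (93.0/4)·[1 + √(1 + 4/(93.0·0.2))]² = 102.8, so 103 per group, as stated.
- Drop-out: 206/0.95 = 216.8, so 217 against the stated 216, a negligible difference.
- With continuity correction, power is about 80% at 103 analysed per arm and 82% at 108. The issue is bias, not sample size.

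**Effect under no true difference.** No withdrawal rate is given, so the number k of failures lost from one arm of 108 is an assumption: 0, 2, 5 or 10. Ten is close to the whole drop-out allowance (0.05 × 216 = 10.8). With true rate p in both arms, the expected spurious difference is p − (108p − k)/(108 − k). For p = 0.4 and k = 5 this is 0.4 − 38.2/103 = 0.029. Type I error comes from simulating the two-sided pooled z-test (400,000 runs per setting).

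| True rate | k = 0 | k = 2 | k = 5 | k = 10 |
|---|---|---|---|---|
| 50%: difference (points) / type I error | 0 / 4.8% | 0.9 / 5.0% | 2.4 / 7.2% | 5.1 / 12.1% |
| 40%: difference (points) / type I error | 0 / 4.9% | 1.1 / 5.5% | 2.9 / 7.9% | 6.1 / 16.3% |
| 30%: difference (points) / type I error | 0 / 5.0% | 1.3 / 5.9% | 3.4 / 9.4% | 7.1 / 23.3% |

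If equal numbers of failures leave both arms, the expected difference under no true effect is zero.

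**A single invented borderline result.** The test is the one-stratum Cochran-Mantel-Haenszel statistic without continuity correction, (N − 1)(ad − bc)² / (product of the four margins).

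- All randomised, 50/108 against 37/108: 215·1404²/(108·108·87·129) = 3.24, p = 0.072.
- Three failures lost from the high-PEEP arm, 50/108 against 34/105: 212·1578²/(108·105·84·129) = 4.30, p = 0.038. With continuity correction p = 0.053.
- Five lost from that arm, 50/108 against 32/103: 5.12, p = 0.024.
- Three lost from each arm, 47/105 against 34/105: p = 0.066.

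**Reach of the safeguard.** The 10% trigger needs more than 21.6 of 216 infants with a missing endpoint. Every case above involves at most ten infants, so it would not fire. Withdrawn infants do not count towards it in any case.

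**The case against.** The strongest counter-argument is that the main route is already closed. Parents who dislike the assigned pressure range, or who react to a failure by asking for it to be stopped, do not remove their infant, because {11b} keeps that outcome in the ITT analysis. This stands. A reader might infer that any parental refusal leads to exclusion, or that {11b} and {20a} flatly contradict each other; neither follows. The sections deal with two acts, ending the intervention and revoking consent. What is missing is a rule for telling them apart, so classification rests on how unblinded staff record a parental request.

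Second, removal may sometimes be required if parents refuse the use of data, and the consent material is not shown. This stands in part. The article does not give it as the reason, and its definition removes every infant with withdrawn consent, not only those whose parents refuse data use. An explicit population definition is also not a detail left to the analysis plan.

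Third, the numbers are extremes. This stands. Nothing in the protocol suggests that only failures, and only in one arm, would be lost. The 5% allowance is for drop-out in general and is not a withdrawal rate. The borderline example is constructed, and its three-loss version depends on the choice of continuity correction.

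Fourth, a reader might infer that harm could be hidden from the data monitoring committee. The text does not support that. Serious events are reported continuously until discharge, possible complications of the intervention go to the coordinating investigator immediately, and the committee receives reports after 50, 100 and 150 patients. Events before a withdrawal could already have passed through that route. The exposure is mainly in the final safety tabulation.

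**Conclusion.** The point holds for formal withdrawal of consent. The ITT and safety populations are defined by consent status after allocation, in an unblinded trial, and the planned sensitivity analysis cannot recover the infants removed.

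The size is unknown. Two one-sided losses leave type I error at 5.0–5.9%. Five raise it to about 7–9% and ten to about 12–23%, assuming 108 per arm, no true effect, true rates of 30–50%, and all losses being failures from one arm. These figures bound the risk and do not predict it. The document permits outcome-related exclusion but does not show that it will occur, so the stronger reading, that the randomised comparison is broken, is not supported. This should be fixed, but it is not a fatal defect.

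**What to change.** - Define ITT as all randomised infants with valid consent at randomisation, analysed in the allocated arm.
- Keep data collected up to withdrawal, so that a recorded 120 h endpoint counts, unless the parents explicitly refuse its use.
- Report removals by arm and timing, and include those infants in a worst/best-case analysis whether or not the 10% trigger is reached.
- Apply the same retention rule to the safety population.
- Reconcile {11b} with {20a} by stating how stopping the intervention, stopping follow-up and refusing data use are recorded, and what each means for the analysis sets.

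The cost is wording in the protocol and analysis plan, possibly one line in the consent form, and a little more analysis. The planned 103 per group and 216 in total do not change.

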### Intervention description {11a}

#### Study intervention

The study intervention is the application of early nasal CPAP/nasal intermittent positive pressure ventilation (NIPPV) with higher PEEP range (6–8 cmH_2_O, intervention group) compared to a lower PEEP range (3–5 cmH_2_O, control group) in the first 120 h of life.

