#### Interventional period

The intervention starts immediately after birth with the first application of nasal CPAP/NIPPV in the delivery room. The study intervention ends at a postnatal age of 120 h. Randomized subjects will receive nasal CPAP/NIPPV immediately after birth using a short nasopharyngeal tube, face mask, or binasal prongs (center specific). The PEEP level will be set within the allocated PEEP range: PEEP_low_ (3–5 cmH_2_O) or PEEP_high_ (6–8 cmH_2_O). During resuscitation, the *initial* PEEP setting in the intervention group must be set 3 cmH_2_O higher than in the control group and will be determined by center guideline prior to study start. The initial PEEP will be *maintained* during the delivery room management and will not be adjusted. Application of PEEP in the delivery room will be provided by a T-Piece resuscitator or a conventional ventilator. The use of a self or flow-inflating bag is not permitted for initial respiratory support. Subjects will be further resuscitated according to the European Consensus Guidelines [4]. Sustained inflation maneuvers can be applied according to local policies for initial stabilization. Primary nasal NIPPV (synchronized or not) can be used in the delivery room. After admission to the neonatal intensive care unit, the PEEP level will be adjusted according to the level of inspired oxygen required to meet the center-specific study SpO_2_ target range within the maximum range of 85–95% throughout the interventional period using the following PEEP titration protocol: (PEEP adjustments should be made on a half-hourly basis to allow the assessment of effects).

Prior to study initiation, we strongly recommend local guidelines for intubation and mechanical ventilation be defined, as well as the indication criteria for surfactant administration that have to be applied equally within both PEEP groups. Suggested intubation criteria within the study are:

FiO_2_ ≥ 0.5 for > 1 h and/or pCO_2_ ≥ 70 mmHg in two consecutive blood gas analysis > 2 h apart after the application of a maximum of 2 surfactant doses (either INSURE (intubate surfactant extubate) or less invasive, i.e., LISA).

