If a study subject requires intubation, decisions on the mode of invasive ventilation, weaning strategies, and extubation are at the discretion of the responsible medical team of the study site with settings and modes identical for both treatment groups. After extubation, the PEEP will be set and adjusted according to the initially assigned PEEP range during nasal CPAP/NIPPV. After the study intervention period, the medical team at each study site will decide on the further mode of respiratory support and weaning strategies.

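### The per-protocol rule selects on the outcome: it removes infants for an event that is itself a primary endpoint, and can remove long-ventilated failures whose care followed the protocol

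*Protocol article*

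**What the plan says.** All references are to the Protocol article.

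- **Statistical analysis {20a}** gives two grounds for leaving the per-protocol population. The first applies when the "PEEP level is not documented or not between 3 and 5" cmH2O in the low arm, or 6–8 cmH2O in the high arm, "for more than 10% of time during the intervention period". The second is "Intubation within the first 10 min after birth and invasive mechanical ventilation for more than 1 h".
- **Interventional period** fixes the denominator of the first rule: "The study intervention ends at a postnatal age of 120 h". It starts with the first nasal support in the delivery room.
- The same part of the protocol leaves invasive ventilation to the site team, "with settings and modes identical for both treatment groups". The assigned range applies again only later: "After extubation, the PEEP will be set and adjusted according to the initially assigned PEEP range during nasal CPAP/NIPPV".
- **Outcomes {12}** counts intubation with more than an hour of ventilation in the first 120 h as a primary-outcome event.
- **Statistical analysis {20a}** makes only the intention-to-treat analysis of the primary outcome confirmatory. The per-protocol analysis of that outcome is planned, but exploratory.

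**The concern.** A per-protocol set should leave out infants who did not receive the assigned treatment. Here both exclusion grounds are tied to whether the infant failed. The second is a subset of the primary endpoint. The first counts all 120 h and does not set aside hours on a ventilator, where the assigned PEEP range does not apply. An infant ventilated for more than 12 h can be classed as non-adherent because the team did what the protocol asks.

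If failures are removed unevenly, the per-protocol comparison can show a difference that does not exist, or hide one that does. If they are removed evenly, a true difference is diluted. In either case a reader comparing the per-protocol result with the intention-to-treat result would take an artefact of the set's definition for information about adherence.

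**Working it through.** **Inputs from the documents.** Planned event rates are 50% (low PEEP) and 30% (high PEEP), with 103 infants per group, two arms at 1:1 and an intervention period of 120 h.

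**The plan's own figure.** With two-sided 5% significance and 80% power:
- uncorrected n = [1.96·√(2·0.4·0.6) + 0.8416·√(0.25 + 0.21)]² / 0.20² = 93 per group
- with continuity correction, n = (93/4)·[1 + √(1 + 4/(93·0.20))]² = 102.8, so 103

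This matches the protocol, so 50%, 30% and 103 are used below.

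**Step 1: the 10-minute exclusion.** It requires ventilation for more than 1 h, starting within 10 minutes of birth. Any such infant meets the first primary-outcome criterion, so all infants removed are failures. The effect is small. Removing an assumed 5% of each arm gives (0.50 − 0.05)/(1 − 0.05) = 47.4% in both arms under no effect. Removing 10% of one arm and 5% of the other gives 44.4% against 47.4%.

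**Step 2: the 10% rule.** 0.10 × 120 h = 12 h. No ventilator PEEP lies in both 3–5 and 6–8 cmH2O. For an infant ventilated for more than 12 h, who is necessarily a failure, there are two cases:
- the common ventilator PEEP lies in one arm's range, so such infants are removed from the other arm only
- it lies between 5 and 6 cmH2O, or is not documented, so such infants are removed from both arms

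**Step 3: size.** Let f be the share of an arm's failures removed. The documents do not give f, so it is assumed over a range. The per-protocol rate is p(1 − f) / [p(1 − f) + (1 − p)]. For p = 0.50 and f = 0.4 this is 0.30/0.80 = 37.5%.

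| f (assumed) | 0.2 | 0.3 | 0.4 | 0.6 |
|---|---|---|---|---|
| No true effect, one arm affected: its rate (other arm 50%) | 44.4% | 41.2% | 37.5% | 28.6% |
| Spurious difference, points | 5.6 | 8.8 | 12.5 | 21.4 |
| Chance of p < 0.05 | 12% | 23% | 40% | 82% |
| True 50% v 30%, low arm affected: difference, points | 14.4 | 11.2 | 7.5 | −1.4 |
| True 50% v 30%, high arm affected: difference, points | 24.5 | 26.9 | 29.5 | 35.4 |
| True 50% v 30%, both arms affected: difference, points | 18.9 | 18.1 | 17.0 | 13.9 |

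The chance of p < 0.05 is for a two-sided two-proportion z-test (normal approximation), starting from 103 per arm and losing 103 × 0.5f infants from the affected arm. If the same f applies to both arms under no true effect, the two rates are equal and there is no spurious difference.

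**The case against.** - **The analysis is exploratory.** This stands. No conclusion, significance level or sample size rests on the per-protocol set, and in a superiority trial it is not co-primary.
- **The size is not established.** This also stands. A reader might infer that the rule will produce a false effect as large as the planned 20 points. That needs about 60% of failures to be ventilated beyond 12 h and all of them to be removed from the same arm. The documents give neither figure. There are six centers and randomization is stratified by center. If some sites ventilate within one range and others within the other, exclusions fall on both arms and may largely cancel under the null.
- **Identical settings need not mean one fixed PEEP.** The team has discretion, so PEEP may vary between infants and over time. The intervention is defined as nasal support, and the section on continuous documentation names CPAP and NIPPV pressures, so the rule could be read as covering non-invasive hours only. That reading is sensible, but the rule does not state it. Its denominator is the whole intervention period, and undocumented hours count against the infant.
- **Infants weaned early or who die.** A reader might infer that these are removed too, for lack of recorded PEEP. The documents do not say how such hours count or how often they arise, and they describe no step off respiratory support before 120 h. Early-weaned infants would mostly be successes, so their removal would act in the opposite direction. The point does not rest on them.
- **This is detail for the analysis plan.** Only in part. The protocol states the rule, its threshold, its denominator and the 10-minute exclusion, and these are what need correcting.
- **Excluding infants with almost no exposure is a familiar convention.** True, and Step 1 shows a small effect. But the criterion used is an endpoint event.

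**Conclusion.** The point holds. The 10-minute exclusion removes only failures; this follows from the text without assumption. The 12 h rule, as worded, can remove failures ventilated for more than 12 h from one arm or both, although care followed the protocol. This rests on ventilated hours counting in the denominator, as the wording implies.

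The per-protocol estimate may therefore be biased, with size and direction unknown. Under no true effect, the spurious difference is 5.6 to 21.4 points for f from 0.2 to 0.6 with one arm affected, and zero with both affected equally. In the latter case a true 20-point effect shrinks to about 17 points at f = 0.4 and 14 at f = 0.6. All values of f are assumed. The documents do not support a claim that a large false effect will occur, or in which direction. The confirmatory intention-to-treat analysis is untouched, so this should be corrected but does not threaten the trial's main conclusion.

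**What to change.** Reword the per-protocol definition, in the protocol or the analysis plan, before the data are analysed:

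1. Apply the 10% rule only to hours when the infant is alive and on non-invasive CPAP/NIPPV, before the first primary-outcome event, with those hours as the denominator. Hours on invasive ventilation, and any hours off support or after death, then do not count as deviations.
2. Remove the 10-minute intubation exclusion from the main per-protocol set, or report it only as a separately labelled subset. State that an infant with no qualifying non-invasive hours has no deviation under item 1.

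The cost is wording and slightly more programming on PEEP data already recorded hourly. Clinical care, sample size and the confirmatory analysis do not change.

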### Sample size {14}

Based on a pre-study survey among participating centers and the results of the AMV study [14], we expect 50% primary endpoints within the control group (lower PEEP level). The intervention will be regarded as being successful if it lowers the rate of the primary endpoints to 30%. This follows the expectations within similar studies [15]. To lower the rate of primary endpoints from 50 to 30% and to confirm this via Cochran-Mantel-Haenszel test (level of significance = 0.05, power = 80%), a sample size of 103 patients per group will be needed. To account for 5% drop outs, an overall sample size of 216 patients have to be recruited and treated within the study.

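### The primary test is worded as a Cochran-Mantel-Haenszel test stratified by treatment; on its workable reading it omits the randomisation strata, and the plan does not name which of two intention-to-treat tests is confirmatory

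*Protocol article*

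**What the plan says.** Three statements under Statistical analysis {20a} bear on the primary comparison.

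- The main test: "The analysis of the primary endpoint will be done by Cochran-Mantel-Haenszel test stratified for treatment groups".
- A second test of the same endpoint: "The primary endpoint will be re-evaluated by Cochran-Mantel-Haenszel test adjusted for gestational age group" and center, with the proviso "If the final number of centers does not allow adjustment for single centers, centers will be grouped". The justification for any grouping is left to the statistical analysis plan (SAP).
- The confirmatory rule: only the analysis of the primary outcome in the intention-to-treat population is "confirmatory on a level of significance of 0.05". The per-protocol analysis and the secondary endpoints are named as exploratory.

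Under Randomization and allocation concealment: "Randomization lists will be stratified by center and gestational age". Recruitment {15} gives 6 centers, and there are two gestational-age groups, so the lists form 12 strata.

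Sample size {14} also names a CMH test, with "level of significance = 0.05, power = 80" per cent, and expects 50% failures in the lower-PEEP arm against 30% in the higher-PEEP arm. It gives no strata and no stratum-specific rates.

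**The concern.** In a CMH test the stratifiers are the variables held fixed, and the comparison is made within them. Naming treatment as the stratifier leaves nothing to compare. If the sentence instead means a plain comparison between arms, the test that appears confirmatory leaves out both factors that the randomisation balances. When those factors predict the outcome, an unstratified test after stratified randomisation uses too large a variance, so it is conservative and less powerful than it could be.

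The protocol then describes two CMH tests of the same endpoint, and its confirmatory sentence fixes the outcome, the population and the alpha but not the test. The trial is unblinded, and the SAP need only be written before the end of the study and the completion of data monitoring. The single test on which the claim rests should therefore be beyond dispute in the protocol.

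**Working it through.** **Inputs from the protocol article.** Failure rates 50% and 30%, alpha 0.05, power 80%, 103 per group, 216 in total with 5% dropout, 1:1 allocation, 6 centers, 2 gestational-age groups. Sidedness is not stated.

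**1. The plan's own sample size.** With d = 0.20 and mean rate 0.40, two-sided:

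n = [1.960 × √(2 × 0.40 × 0.60) + 0.842 × √(0.50 × 0.50 + 0.30 × 0.70)]² / 0.20² = 93.0

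With the continuity correction:

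n′ = (n/4) × [1 + √(1 + 4/(n × d))]² = (93.0/4) × [1 + √(1 + 4/18.6)]² = 102.8, rounded up to 103

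This matches the stated 103. The one-sided versions give 74, or 83 with the correction, so the plan is two-sided. For dropout, 206 × 1.05 = 216.3 and 206/0.95 = 216.8, in line with 216. The stated size is therefore that of an unstratified, continuity-corrected comparison of two proportions.

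**2. The literal reading.** For each table with arm sizes n1 and n0, m events and total t, the CMH variance term is n1 × n0 × m × (t − m) / [t² × (t − 1)]. With treatment as the stratum, one arm size is 0 in every table, so every term is 0 and the statistic is undefined.

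**3. The workable reading.** A single-table CMH test is practically the Pearson chi-square. Its power at 103 per group, without continuity correction, is

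Φ{[0.20 × √103 − 1.960 × √0.48] / √0.46} = Φ(0.99) = 83.9%

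With the continuity correction used in step 1, 103 per group gives about the planned 80%.

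**4. Unstratified against stratified.** The document does not say how strongly center and gestational age predict failure, so this strength is assumed over a range. Simulation set-up: 206 infants, 12 strata of equal expected size, permuted blocks of 2 or 4, marginal rates 50% and 30% (50% in both arms under the null), two-sided 0.05, no continuity correction, 8,000 runs per setting. The standard error of a 5% rate is √(0.05 × 0.95/8000) = 0.24 points.

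| Assumed strength: gestational-age odds ratio; center SD (logit) | Power, unstratified | Power, stratified | Type I, unstratified | Type I, stratified | Type I, either test |
|---|---|---|---|---|---|
| 1; 0 (not prognostic) | 83.9% | 83.8% | 4.4% | 4.8% | 4.9% |
| 2; 0.3 | 85.2% | 86.0% | 4.3% | 4.9% | 5.0% |
| 3; 0.5 | 85.5% | 87.7% | 3.6% | 5.2% | 5.2% |
| 4; 0.8 | 86.1% | 90.2% | 2.9% | 5.1% | 5.1% |

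A separate simulation of 4,000 runs per setting, from weaker to stronger strata, gave unstratified type I error of 4.2%, 3.4% and 2.7% against 5.0%, 5.1% and 4.6% stratified. Power was 84.9%, 84.5% and 84.7% against 85.7%, 87.6% and 89.1%.

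**5. How often the choice of test matters.** In the first simulation, the two tests disagreed on significance in 0.9% to 4.1% of trials under the planned effect and in 0.6% to 2.2% under the null.

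**The case against.** The intended meaning can be recovered. Adverse event reporting and harms {22} uses the same turn of phrase for safety rates, where it can only mean rates shown by arm. The next sentence on the primary endpoint contrasts the first test with an adjusted one, and the sample size is that of a comparison without strata. This stands. A reader might infer that the trial has no primary test that can be run; the documents support only that the sentence is wrong as worded.

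A reader might also infer that the trial is underpowered. It is not: the unstratified test has about 84% power. The loss is relative to the stratified test and vanishes if the strata are not prognostic. Nor can both complaints hold at once, since an undefined test belongs to the literal reading and a loss of power to the workable one.

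A third tempting inference is that two candidate p-values inflate the false-positive rate. The order of the sentences, and the description of the second test as a re-evaluation, point to the first as confirmatory. Even free choice between them gives at most about 5.2%, no more than the stratified test's own simulated rate of 5.2%.

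Finally, the center-grouping clause is conditional, applies to the re-evaluation and defers its justification to an SAP that is not shown. The secondary tests are declared exploratory. Neither is an error.

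What remains is a misworded definition of the only confirmatory analysis, the omission of the randomisation strata from it, and a confirmatory sentence that does not name its test.

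**Conclusion.** The point holds as a fault of specification with a modest efficiency cost. The wording is wrong as written. On the workable reading the apparent primary test is valid and meets the planned power, but it leaves out the randomisation factors. If those are prognostic it is conservative, with type I error of about 2.7% to 4.4% across the settings tried, against about 5% for the stratified test. It gives up 0 to about 4 points of power.

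These figures rest on assumed stratum strength, equal expected stratum sizes, blocks of 2 or 4, and tests without continuity correction. The 4.4% comes from the setting with no prognostic strata, where the stratified test also fell slightly below 5% (4.8%), so it should not be put down to the omitted strata. The size of the effect does not call the trial's validity or its sample size into question.

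**What to change.** Replace the sentence defining the primary analysis with:

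> The single confirmatory analysis is the two-sided CMH test of treatment in the intention-to-treat population, stratified by gestational-age group and center as randomised, reported with the Mantel-Haenszel risk difference and 95% CI.

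Label the unstratified comparison as supportive. If centers may be grouped, fix the rule in the SAP without reference to outcome data by arm, since the grouping would then affect the confirmatory test.

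The cost is one sentence in the protocol, carried into the SAP before outcomes are examined by arm. It needs no new data and no change to the sample size or the secondary tests.
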